### Study population

#### Derivation phase

Study population will include neonates with known cardiovascular status including newborns with and without SHD. Working definition of SHD is any cardiovascular anomaly that will require longitudinal follow-up or intervention based on current practice. This broad definition of SHD parallels the overall goal of this investigation: to develop a screening tool aiming for high sensitivity and flexible performance across the diverse and heterogeneous morphological and functional spectrum of cardiovascular anomalies in newborns.

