### Study procedure

#### Patient enrolment

For the derivation phase newborns without SHD will be enrolled at the time of discharge from Ob/Gyn programme and newborns with SHD will be enrolled at the time of cardiovascular examination. For the validation phase consecutive newborns will be enrolled at the time of discharge from Ob/Gyn unit.

*
Graphical abstract
* summarizes the study pipeline.

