#### Derivation phase

After screening of eligible patients, written informed consent will be obtained from parents or caregivers.

The first echocardiographic evaluation will take place at a post-natal age < 30 days. Age at recording and echocardiographic evaluation will be planned not before 7 days of post-natal life to allow completion of proper cardio-circulatory transition in the healthy newborns (i.e. ductal closure, pulmonary vascular remodelling, foramen ovale physiologic shunt). The echocardiogram will be linked to an anonymous identifier which will be used to link the exam to the patient without breaching patient privacy. The examination will be digitally stored and transferred to the Echocardiography Study Core Lab for formal revision. The cardiovascular neonatal status will be appropriately labelled as being with or without cardiovascular abnormalities.

Heart sound will be digitally recorded using as acquisition device Littmann Core Stethoscope (Eko Software) (3 M Company, Minnesota/USA). Cardiac sound tracings will be recorded and stored in wav format and encrypted transferred to the Bioengineer Research Unit for further elaboration. Cardiovascular neonatal status will be un-blinded to the Bioengineer Research Unit to allow for proper handling of classifier training.

The details of the acquisition method are as follows:

Acquisition device: Littmann Core Stethoscope (Eko Software) (3 M Company, Minnesota/USA)No filtering of raw signal will be applied. Specifically, the Stethoscope filtering and volume equalization will be set at 0 through the Eko interface. The only residual filter will be the analogue filter related to the stethoscope membrane's elastic properties. This is to minimize the impact of the specificities of the Eko Software on the sound samples and therefore on the training of the classifier.Position of the auscultation: mid precordium, 1 cm medial and 1 cm above papilla mammae (see Online Supplementary Material). Gentle pressure is applied on chest, spontaneous breathing, patients will be kept as calm as possible using maternage without any sedation. Sound sampling will be performed in a calm environment (outpatient clinic or neonatal intensive care unit). A total of three recordings per patient are anticipated to improve sound quality. Sampling tracings with abnormal acoustic contamination (intense crying, environmental noises, friction rubs) will be discarded.Average recording duration: 15 s

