**Figure 1 ztag103-F1:**
[figure not shown]
Diagram of validation phase. Each newborn with blinded cardiovascular status will undergo clinical screening as indicated by current practice and regulations and digital screening using the DI_SOUND algorithm. Gold standard evaluation will be comprehensive echocardiography. Pertinent diagnostics are reported at the bottom.

Cost-effectiveness validation (Aim 3)

Aim 3 will evaluate the potential impact of digital screening on healthcare utilization and costs compared with current standard clinical screening. The target population will consist of newborns at low risk for SHD, with no prior indication for cardiovascular examination, in order to approximate the prevalence of undiagnosed cardiovascular abnormalities in the general newborn population.

For the purpose of this analysis, outcomes will be explicitly defined as follows:

Prevented unnecessary examinations: cases in which (healthy) newborns with a positive result at standard clinical screening but a negative result at digital screening are subsequently confirmed to be free of SHD (i.e. false positives avoided by digital screening).Missed necessary examinations: cases in which newborns (with SHD) with a positive result at standard clinical screening but a negative result at digital screening are subsequently diagnosed with SHD (i.e. false negatives introduced by digital screening).

A decision-analytic modelling framework will be developed to compare digital screening with standard clinical practice. Model inputs will include estimates of SHD prevalence, test performance characteristics (sensitivity and specificity of both screening strategies), and downstream diagnostic pathways. Cost estimates will be derived from national diagnosis-related group reimbursement schedules to reflect healthcare system expenditures associated with confirmatory examinations and missed diagnoses.

To account for parameter uncertainty and variability, a probabilistic sensitivity analysis will be conducted using Monte Carlo simulation. This approach will allow repeated sampling from predefined distributions of key parameters (e.g. prevalence, sensitivity, specificity, and costs) to generate distributions of expected costs and outcomes for each screening strategy. The primary outcome will be the incremental cost-effectiveness of digital screening compared with standard clinical screening, expressed in terms of cost per unnecessary examination avoided and cost per missed SHD case.

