### Statistic plan

Between-group comparisons for clinical and outcome variables will be performed using independent samples *t*-test, Wilcoxon rank sum test, chi-square analysis, or Fisher's exact test using appropriate variable-specific denominators.

For experimental design Aim 1, limited data are available to build up a reliable power calculation at this stage, but we expect to enrol 600 patients with 2:1 diseased:healthy newborn ratio in this experimental phase. The rationale behind the ratio is due to the higher variability of diseased subjects with respect to the healthy ones.

Specific potential classifiers will be studied in the spectral features, cepstral features, and time-domain features. Dataset will be split into training set, validation set, and test data set. The performance of the classifiers will be evaluated using K-Fold cross-validation. Different folding levels will be tested: 10-fold, 5-fold, and LOOCV, aiming for >95% sensitivity and >90% specificity. The numerosity of the sample we target will allow to estimate the target sensitivity and specificity with sufficient accuracy, in particular with the target numerosity we can estimate a 95% confidence interval of ±2% in the sensitivity estimate and ±4% for the specificity estimate.

Gini importance for Random Forest classifiers will be used as a tool to validate parameters with least predictive contribution. Gini importance can be defined as the probability of making a false classification of a randomly chosen record if it were randomly labelled in the class distribution. During the training of the decision trees of the random forest, each tree is a set of internal nodes and leaves. In the internal node, selected feature is used to make decision of dividing the dataset into two separate splits. Selection of the feature is done with Gini impurity criterion. The feature that brings the highest decrease of Gini impurity is selected for the internal nodes. Even after training, how each feature decreases the impurity can be calculated and accepted as the importance of that feature.

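### Derivation tracings are discarded by judgement while SHD status can be known to everyone described as handling them, so the Aim 1 sensitivity and specificity may be optimistic by an unknown amount, possibly zero

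*Protocol article*

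**What the plan says.** All references are to the protocol article.

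- **Status is known at entry.** Study population, Derivation phase: "Study population will include neonates with known cardiovascular status including newborns with and without SHD".
- **Entry routes differ by status.** Under Patient enrolment, healthy derivation newborns enter at discharge from the maternity unit, whereas "newborns with SHD will be enrolled at the time of cardiovascular examination".
- **Recordings and discards.** The acquisition details under Study procedure, Derivation phase, say "A total of three recordings per patient are anticipated to improve sound quality" and then "Sampling tracings with abnormal acoustic contamination (intense crying, environmental noises, friction rubs) will be discarded". No noise threshold, assessor or blinding is given for the discard.
- **Engineers are un-blinded.** Same section: "Cardiovascular neonatal status will be un-blinded to the Bioengineer Research Unit to allow for proper handling of classifier training".
- **Aim 1 size and target.** Statistic plan: "we expect to enrol 600 patients with 2:1 diseased:healthy newborn ratio", with cross-validated performance "aiming for >95% sensitivity and >90% specificity" and stated 95% confidence intervals of ±2% for sensitivity and ±4% for specificity.
- **Contrast in validation.** Figure 1 legend: "Each newborn with blinded cardiovascular status will undergo clinical screening as indicated by current practice and regulations and digital screening".

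**The concern.** Training a classifier needs the labels. Deciding whether a tracing is usable does not. The article does not separate the two steps: the discard is a judgement, and both groups described as handling derivation tracings can know the newborn's status when it is made.

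The judgement can then lean on the label without anyone intending it. An unexpected sound in a newborn known to be healthy is easily put down to noise. A tracing from a newborn with known SHD that sounds unremarkable may be set aside as poor. Each choice removes a recording that the classifier would probably get wrong. The Limitation section itself accepts that some severe lesions have few acoustic signs.

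At stake is whether the Aim 1 figures, which are compared with the >95% and >90% targets, describe recordings as they will be met in use. Selection made before the split affects training, validation and test sets alike, so neither K-fold nor leave-one-out cross-validation would reveal it. Tracings deleted at this stage cannot be recovered later.

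**Working it through.** **Inputs from the article:** 600 derivation newborns at 2:1, hence 400 with SHD and 200 healthy; targets of 95% sensitivity and 90% specificity; three recordings per newborn. **Not given:** the discard rate and how far it depends on the label or on how hard a tracing is to classify. These are assumed below.

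**1. The plan's own precision.** Half-width = 1.96 × √(p(1−p)/n).
- Sensitivity: 1.96 × √(0.95 × 0.05/400) = 2.1 points.
- Specificity: 1.96 × √(0.90 × 0.10/200) = 4.2 points.

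The stated ±2% and ±4% reproduce after rounding.

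**2. Dropping a share of would-be errors only, at the target values.**
- Sensitivity 95%: 400 × 0.05 = 20 misses. Dropping a quarter (5) gives 380/395 = 96.2%, a shift of +1.2 points, which is inside ±2.
- Specificity 90%: 200 × 0.10 = 20 false positives. Dropping a quarter (5) gives 180/195 = 92.3%, a shift of +2.3 points, which is inside ±4.

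**3. Discarding spread over all newborns.** Let d be the discard probability for newborns the classifier would get right, and r × d the probability for those it would get wrong. Then apparent performance = p(1−d) / [p(1−d) + (1−p)(1−rd)].

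| d | r | Sensitivity (true 95%) | Specificity (true 90%) |
|---|---|---|---|
| any | 1 | 95.0% (0) | 90.0% (0) |
| 10% | 2 | 95.5% (+0.5) | 91.0% (+1.0) |
| 20% | 2 | 96.2% (+1.2) | 92.3% (+2.3) |
| 20% | 3 | 97.4% (+2.4) | 94.7% (+4.7) |

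Discarding unrelated to classifiability (r = 1) gives no bias at any rate. Only the most extreme row exceeds the stated ±2 and ±4.

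**4. Effect of three recordings.** Steps 2 and 3 remove whole newborns, which requires all three tracings to be discarded. Suppose each tracing of a missed newborn had a one-in-four chance of being discarded, independently. All three would be lost with probability (1/4)³ = 1/64. The expected loss is 20/64 = 0.31 newborns, giving 380/399.69 = 95.1%. Discards within a newborn are probably correlated, since a crying infant tends to spoil all three, so at that discard chance the figure lies between 95.1% and 96.2%. If performance is counted per tracing instead, this protection does not apply: the article says the number of leave-one-out folds equals the number of records, and a record may be a tracing.

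**The case against.** Much of the case on the other side stands.

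- **Who discards is not stated.** A reader might infer that un-blinded staff do it. The article does not say so. The discard sentence sits among the bedside acquisition details, and the engineers are given no discard role. What stands is narrower: everyone described as handling the tracings can know the label, and nothing described prevents its use.
- **The full protocol may settle it.** The article refers to a supplement that is not shown. If that names a label-blind rule, one sentence answers the point. The point rests on what the article does state, namely a judgement-based discard together with known status and un-blinding. The article mentions blinding elsewhere, in validation.
- **The listed reasons are external noise.** A quiet, normal-sounding SHD tracing gives little ground for calling it contaminated, so the mechanism is more plausible for specificity than for sensitivity. This weakens the sensitivity argument without removing it.
- **Comparison with ±2 points.** A reader might infer that the bias must exceed the stated precision, for example by taking a true sensitivity of 90%, where dropping a quarter of 40 misses gives 360/390 = 92.3%. But the ±2% belongs to 95%. At 90% the half-width is 1.96 × √(0.9 × 0.1/400) = 2.9 points, so a 2.3-point shift does not exceed it.
- **Aim 2 contains the consequence.** An independent cohort of about 1900 newborns of unknown status would expose optimistic Aim 1 figures rather than inherit them. This is correct and limits the importance of the point.

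**Conclusion.** The point holds as a risk of optimistic Aim 1 estimates. It is not a demonstrated bias. As described, the selection of derivation recordings can depend on the SHD label, and cross-validation would not show it. The article does not support the stronger conclusion that both estimates are inflated: it gives neither the assessor nor the discard rate, and label-independent discarding gives no bias.

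The size is unknown. Under the assumed discard rates it runs from zero to +2.4 points for sensitivity and +4.7 points for specificity. A moderate case, with a quarter of the missed newborns dropped at a true 95%, gives 96.2%, and less once the three recordings per newborn are allowed for. The Aim 2 estimates are protected by their independent cohort. What remains exposed is the choice of features and model, and the judgement against the >95% and >90% targets before validation begins. Because deleted tracings cannot be restored, this is worth settling before collection.

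**What to change.** 1. Upload every recorded tracing; delete none at the bedside.
2. Have the engineering unit apply one fixed signal-quality rule, preferably automatic, before it receives SHD labels.
3. Freeze the list of usable tracings, and only then release the labels for training.
4. Apply the identical rule to the validation recordings.
5. Report the number of discarded tracings, and of newborns left without a usable one, by SHD status.

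This mainly changes the order of two existing steps. It needs no extra newborns, and no new staff if the engineering unit applies the rule before un-blinding. The cost is that the rule must be specified and coded in advance, and labels are released slightly later.

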Phonocardiographic signals will be stored as wav files in an encrypted cloud system to be transferred for further analysis (*Graphical abstract*). Tracings will undergo preliminary processing to remove background noise, and will be segmented to generate sound samples of homogeneous suitable tuned duration. As the last step of the preprocessing, the filtered records will be normalized for preventing inhomogeneity in the extracted features. Data analysis will be then implemented based on handcrafted feature extraction. The main objective of feature extraction is to identify a small number of representative features characteristic properties of a sound sample, that replace the high-dimensional raw signals still preserving its informative content with respect to the phenomenon under investigation. Relevant features are then fed to the classification algorithm to discriminate between healthy and abnormal subjects. Multiple different techniques will be used for feature extraction in sound signals, and can be loosely grouped into frequency-domain techniques, time-frequency domain techniques, linear predictive coding, and time-domain techniques. Each of these techniques provides descriptors of potentially relevant properties of the sound sample, which can be used as features or further processed to extract higher level characteristics of the signal (such as systole and diastole variability). To maximize the robustness of our results to less-than-ideal acquisition conditions, we will train the classifiers using features from all the above-mentioned domains and will perform a feature selection procedure to select those features which are mostly correlated to the outcome of interest. Standard machine learning models will be preferred, as simpler models tend to perform more robustly when training data is limited. Neural networks may be implemented if they will exhibit superior results with respect to standard models on the available dataset without clear signs of overfitting. Following the standard best practice, the dataset will be split into training set, validation set and test data set. For evaluating the performance of classifiers, K-Fold cross-validation with different fold numbers will be used: 10-fold, 5-fold, and Leave-One-Out-Cross-Validation (LOOCV). In LOOCV, the number of folds is equal to number of records. Gini importance for Random Forest classifiers will be used as a tool to validate parameters with least predictive contribution. Once a proper classifier has been trained a post training analysis to determine the most relevant features will be conducted. The purpose of this analysis is to investigate to which extent each feature is contributing to the selection of one class with respect to the other. Techniques for feature relevance estimation based on SHAP values, or permutation analysis will be applied also with the aim of providing a proper explanation to the model decision (*Graphical abstract*).

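### Leave-one-out cross-validation is defined by record, not by newborn, so the Aim 1 sensitivity and specificity can be inflated if more than one record per baby is kept

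*Protocol article*

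**What the plan says.** All references are to the protocol article.

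- **Recordings per newborn** (Derivation phase, acquisition method): "A total of three recordings per patient are anticipated to improve sound quality". Contaminated tracings are discarded.
- **Segmentation** (Derivation phase): the tracings "will be segmented to generate sound samples of homogeneous suitable tuned duration". The number of samples per tracing is not given.
- **Meaning of record** (same paragraph): the word is used for processed sound tracings, as in "the filtered records will be normalized for preventing inhomogeneity in the extracted features".
- **Leave-one-out rule** (same paragraph): "In LOOCV, the number of folds is equal to number of records".
- **Other splits** (same paragraph): 10-fold and 5-fold cross-validation are also planned, and "the dataset will be split into training set, validation set and test data set". No splitting unit is given for any of these.
- **Targets** (Statistic plan): "Different folding levels will be tested: 10-fold, 5-fold, and LOOCV, aiming for >95% sensitivity and >90% specificity".
- **Sample and precision** (Statistic plan): "we expect to enrol 600 patients with 2:1 diseased:healthy newborn ratio in this experimental phase". The stated 95% confidence interval is ±2% for sensitivity and ±4% for specificity.

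The article does not say that all recordings and segments of one newborn stay in the same fold or the same set.

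**The concern.** The label is the newborn's echocardiographic status, so all records of one baby carry the same label. They are also alike for reasons unrelated to disease: the same chest, the same single mid-precordial site and the same device. When one record is left out and its siblings stay in training, a flexible classifier can recognise the baby and return its known label. The held-out result then measures re-identification as well as disease detection.

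Two things are at stake in Aim 1. First, the sensitivity and specificity compared with the targets may be too high. Second, the choice of model may be distorted. The Derivation phase section prefers standard models and admits neural networks if they do better without clear signs of overfitting. Record-level folds weaken that safeguard, because memorising babies looks like better performance and does not show up as error in the held-out records.

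**Working it through.** **1. The plan's own precision.** Inputs from the Statistic plan: 600 newborns at 2:1, so 400 diseased and 200 healthy; target sensitivity 0.95 and specificity 0.90. Half-width = 1.96 × √(p(1−p)/n).

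| Unit counted | Sensitivity, p = 0.95 | Specificity, p = 0.90 |
|---|---|---|
| Newborns (n = 400; 200) | 1.96 × √(0.0475/400) = ±2.14% | 1.96 × √(0.09/200) = ±4.16% |
| Records, 3 each, taken as independent (n = 1,200; 600) | ±1.23% | ±2.40% |

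The stated ±2% and ±4% reproduce with the newborn as unit and not with the record as unit. The precision statement and the leave-one-out rule therefore use different units.

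**2. Number of folds.** By newborn, leave-one-out has 600 folds. By record, with all three recordings kept, it has 3 × 600 = 1,800, and more if segments are the records.

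**3. How often a held-out record has a sibling in training.** With m records per newborn split at random by record into k folds, the probability of at least one sibling in training is about 1 − (1/k)^(m−1). For m = 3:

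- Leave-one-record-out: 100%; both siblings are always in training.
- 10-fold, if split by record: 1 − (1/10)² = 99%.
- 5-fold, if split by record: 1 − (1/5)² = 96%.

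The last two lines are conditional, because the article does not give the unit for those schemes.

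**4. Possible size of the inflation.** The document gives no within-newborn correlation of sound features, so this is an assumed range. Simulation: 400 + 200 newborns, 3 records each, 20 features (assumed), no true difference between classes, 1-nearest-neighbour classifier. Entries are sensitivity/specificity.

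| Within-newborn correlation (assumed) | Leave one record out | Leave one newborn out |
|---|---|---|
| 0 | 66%/34% | 66%/33% |
| 0.3 | 67%/35% | 66%/34% |
| 0.5 | 74%/46% | 68%/33% |
| 0.8 | 98%/97% | 68%/33% |

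With a 2:1 mix, chance for this classifier is about 67%/33%, which is what the newborn-level column shows. At 0.8, leakage alone exceeds both targets. At 0.5 it is clearly visible but far short of them.

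**5. Effect on model choice.** With a moderate true signal in 3 features and correlation 0.8 (both assumed), nearest-neighbour gives 99%/98% by record and 75%/43% by newborn. A linear model in 10-fold cross-validation gives 75%/74% by record and 75%/73% by newborn. Record-level folds would choose nearest-neighbour; newborn-level folds would choose the linear model, which is the better one here.

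**The case against.** **The word may be generic.** The leave-one-out sentence reads like a textbook definition, and the description of Gini importance in the Statistic plan uses the word just as loosely. Three recordings anticipated for sound quality could mean retakes from which one is kept, and the stated aim is to separate healthy from abnormal subjects. This stands as a possible reading, and it makes the concern conditional on more than one record per newborn being kept. The text does not say that only one is kept. The same paragraph uses the word for sound tracings, and segmentation could multiply samples even from one recording.

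**Grouping may be left to the full protocol.** This stands for 10-fold, 5-fold and the training/validation/test split, where the article is silent. It does not stand for leave-one-out, where the article does state a unit.

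**Stronger readings that the document does not support.**

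- A reader might infer that the planned Aim 1 confidence intervals are wrong because records are not independent. Step 1 shows the opposite: the stated precision counts newborns.
- A reader might treat the >95%/>90% figures as a gate to the validation cohort of about 1,900 newborns. The article presents them as aims and calls the phases sequential; it makes no such condition.
- A reader might infer that feature selection is done once on all the data, outside the folds. The article does not say where it is done.
- A reader might take inflation as certain. It depends on the classifier and the correlation, and nearest-neighbour is among the classifiers most prone to leakage.

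**The damage is contained.** Aim 2 uses an independent cohort with errors defined per newborn. This stands: its estimates are not directly biased.

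**Conclusion.** The concern holds in a limited form. As written, the leave-one-out rule separates records rather than newborns, and it disagrees with the unit behind the plan's own precision statement. If more than one record per newborn enters the analysis, the Aim 1 sensitivity and specificity can be inflated and a model that memorises babies can be preferred. For the other splits this is a risk, not a stated fact.

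The size is unknown from the document. It ranges from almost nothing at low within-newborn correlation, or with a linear model, to enough to exceed both targets without any disease signal (nearest-neighbour, correlation 0.8). The correlations, the feature count and the choice of classifier in that range are assumptions. The harm is an optimistic Aim 1 estimate and possibly a worse model carried into Aim 2, where the independent cohort would show its weakness only after enrolment.

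**What to change.** Make the newborn the unit throughout the derivation phase:

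- Replace leave-one-record-out with leave-one-newborn-out.
- Keep all recordings and segments of a newborn in one fold and in one of the training, validation and test sets, for every split including 10-fold and 5-fold.
- Carry out feature selection and tuning within the training folds.
- Score sensitivity and specificity once per newborn, with a stated rule for combining that baby's recordings and segments.

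The cost is about one sentence in the plan and a grouped split in the code. Apparent Aim 1 performance may be less favourable. No sample-size change is needed: with 400 and 200 newborns as the unit, the stated ±2% and ±4% stand.
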